# PATHOS: a phase II/III trial of risk-stratified, reduced intensity adjuvant treatment in patients undergoing transoral surgery for Human papillomavirus (HPV) positive oropharyngeal cancer

**DOI:** 10.1186/s12885-015-1598-x

**Published:** 2015-08-27

## Abstract

**Background:**

Human papillomavirus-positive oropharyngeal squamous cell carcinoma is increasing in incidence worldwide. Current treatments are associated with high survival rates but often result in significant long-term toxicities. In particular, long-term dysphagia has a negative impact on patient quality of life and health. The aim of PATHOS is to determine whether reducing the intensity of adjuvant treatment after minimally invasive transoral surgery in this favourable prognosis disease will result in better long-term swallowing function whilst maintaining excellent disease-specific survival outcomes.

**Methods/Design:**

The study is a multicentre phase II/III randomised controlled trial for patients with biopsy-proven Human papillomavirus-positive oropharyngeal squamous cell cancer staged T1-T3 N0-N2b with a primary tumour that is resectable via a transoral approach. Following transoral surgery and neck dissection, patients are allocated into three groups based on pathological risk factors for recurrence. Patients in the low-risk pathology group will receive no adjuvant treatment, as in standard practice. Patients in the intermediate-risk pathology group will be randomised to receive either standard dose post-operative radiotherapy (control) or reduced dose radiotherapy. Patients in the high-risk pathology group will be randomised to receive either post-operative chemoradiotherapy (control) or radiotherapy alone. The primary outcome of the phase II study is patient reported swallowing function measured using the MD Anderson Dysphagia Inventory score at 12 months post-treatment. If the phase II study is successful, PATHOS will proceed to a phase III non-inferiority trial with overall survival as the primary endpoint.

**Discussion:**

PATHOS is a prospective, randomised trial for Human papillomavirus-positive oropharyngeal cancer, which represents a different disease entity compared with other head and neck cancers. The trial aims to demonstrate that long-term dysphagia can be lessened by reducing the intensity of adjuvant treatment without having a negative impact on clinical outcome. The study will standardise transoral surgery and post-operative intensity-modulated radiotherapy protocols in the UK and develop a gold-standard swallowing assessment panel. An associated planned translational research programme, underpinned by tumour specimens and sequential blood collected as part of PATHOS, will facilitate further empirical understanding of this new disease and its response to treatment.

**Trial registration:**

This study is registered with ClinicalTrials.gov identifier NCT02215265.

## Background

Oropharyngeal squamous cell carcinoma (OPSCC) is a rapidly increasing disease in the UK and other developed countries as a result of Human papillomavirus (HPV) genotype 16 infection. Currently, over 70 % of OPSCC in Europe is HPV 16 positive [1]. HPV status is a strong and independent prognostic factor for survival, and HPV-positive OPSCC has a 58 % reduction in the risk of death compared to HPV-negative OPSCC [2]. Other factors known to influence prognosis in HPV-positive OPSCC include smoking, particularly current smoking, nodal stage and patient comorbidities [2–4].

Currently, the management of OPSCC is based on the stage of disease as well as clinician and patient preference, irrespective of HPV status. Early stage disease is treated with either surgery or radiotherapy (RT) alone, whilst locally advanced disease requires multimodality treatment with primary chemoradiotherapy (CRT) +/- neck dissection or primary surgical resection followed by post-operative RT/CRT. Severe late toxicities after multimodality treatment are reported in up to 43 % of patients and may be permanent [5]. Patients and their carers report dysphagia to be a primary cause for distress, and patient reported dysphagia independently predicts for poor long-term quality of life (QOL) [6, 7]. Patients with HPV-positive OPSCC tend to be young (mean age 54 years) and fit at presentation [2]. Reducing the adverse impact of treatment on function and maintaining good QOL are therefore of paramount importance in these patients who have good prognosis disease.

### Role of transoral surgery

With the advent of minimally invasive techniques, such as Transoral Laser Microsurgery (TLM) and Transoral Robotic Surgery (TORS), there has been renewed interest in primary surgical treatment for OPSCC as these techniques result in less morbidity when compared to open surgery. There are as yet no prospective randomised data on TLM/TORS for OPSCC but retrospective studies have demonstrated excellent outcomes. A US study of 204 patients with stage III-IV OPSCC treated with TLM and neck dissection found rates of local control (LC), overall survival (OS) and disease-free survival (DFS) to be 97, 86 and 82 % respectively at 3 years, with HPV-positive OPSCC having even better outcomes [8]. Most patients had adjuvant treatment (RT/CRT), which increased toxicity. Single centre data on TLM in the UK is also encouraging. Data from Liverpool on 153 patients with T1-T3 OPSCC (66 % HPV positive) treated with TLM and neck dissection demonstrate 3 year OS of 84.5 %, disease specific survival (DSS) of 91.7 % and DFS of 78.2 %. Patients with HPV-positive OPSCC had a 71 % reduction in the risk of death. 83.6 % of patients received adjuvant treatment. ([name], manuscript submitted). Single institution data also show a functional advantage with upfront transoral surgery compared to primary CRT [9]. A UK study compared swallowing function between 23 patients with locally advanced OPSCC treated with TLM +/- adjuvant therapy and 33 matched patients treated with CRT from a historical cohort and reported improved early swallowing function at 3 months in the upfront surgery group, using 3 different swallowing measures, including the MD Anderson Dysphagia Inventory (MDADI) score [10].

### Adjuvant therapy: risk factors, RT dose and use of chemotherapy

Currently, decisions about adjuvant therapy after surgery are based on the presence of pathological risk factors established more than 20 years ago in studies that included squamous cancers from multiple head and neck anatomical subsites and that did not test for tumour HPV status [11]. These risk factors include surgical margin status, presence of perineural and vascular invasion, number of lymph node metastases and presence of extracapsular spread (ECS) of nodal disease. The relevance of these risk factors in HPV-positive disease has been questioned and the optimum adjuvant treatment protocols for HPV-positive OPSCC are yet to be determined [12].

Adjuvant RT after surgery for advanced head and neck cancers improved LC in the RTOG 73-03 trial [13]. Subsequent studies recommended a minimum dose of 57.6Gy to the primary site and involved nodal areas and doses of up to 63Gy to areas of ECS [14]. However, lower doses of adjuvant RT may be sufficient for HPV-positive OPSCC based on the following: (i) observations that HPV-positive cell lines show increased radiosensitivity compared to HPV-negative cell lines in vitro [15, 16]; (ii) phase II data (ECOG 1308) showing equivalent LC rates at 2 years with reduced dose RT (54Gy in 27 × 2Gy fractions) in patients with HPV-positive OPSCC who achieved a complete response after 3 cycles of induction chemotherapy [17]; (iii) use of lower doses of prophylactic RT (50Gy in 35 × 1.4Gy fractions, equivalent to 43Gy in 2Gy fractions) with no increase in recurrences [18].

The EORTC 22931 and RTOG 9501 Randomised Controlled Trials (RCTs) showed that adjuvant CRT improved LC and DFS compared with adjuvant RT alone in some patients with advanced head and neck cancer [19, 20]. When the results of both studies were pooled, adjuvant CRT significantly improved OS in patients with positive (or ‘involved’) surgical margins and/or presence of nodal ECS [21]. These pathological features are now widely used criteria for adjuvant CRT. There is variation in practice however, particularly around the issue of surgical margins with positive (<1 mm) and close (1-5 mm) margins being grouped together in some studies. A survey of clinical oncologists from 17 UK centres reported that all would recommend adjuvant CRT for positive surgical margins (<1 mm) whilst only 30 % would advocate its use for close margins (1–5 mm) and 88 % for ECS [22]. The relevance of the EORTC 22931 and RTOG 9501 study results should be questioned in the context of HPV-positive OPSCC. Patients in these studies had tumours from multiple head and neck anatomical subsites and the prevalence rate of HPV-positive OPSCC would have been significantly lower than the current rate [1]. Evidence for using adjuvant CRT after transoral surgery for OPSCC is also lacking. A retrospective study of TLM for advanced OPSCC showed that the addition of chemotherapy to adjuvant RT did not improve outcomes even in the presence of ECS, possibly because a high proportion of patients in that study had HPV-positive tumours with already excellent outcomes [8, 12].

### Dysphagia after treatment

There are several factors that may contribute to dysphagia after treatment. Dysphagia after RT has been shown to correlate with increased mean doses of radiation to swallowing-related organs, with a higher mean dose to superior pharyngeal constrictor muscle region and larynx being particularly associated with worse long-term swallowing outcomes [23, 24]. The sigmoidal shape of the normal tissue complication probability curve indicates that increasing mean dose to pharyngeal musculature between 50Gy and 60Gy is a critical point at which risk of long-term dysphagia begins to inflect upwards, suggesting that reducing radiation dose from 60Gy to 50Gy could impart a clinically significant improvement in long-term swallowing outcomes [23]. Adding concurrent chemotherapy to primary or adjuvant RT increases the risk of dysphagia: a systematic review of TORS for OPSCC showed clear demarcation in swallowing outcomes across a variety of outcome measures in patients who received adjuvant RT alone compared to adjuvant CRT [25].

#### Study rationale

Current treatments for HPV-positive OPSCC are associated with high survival rates but often result in significant long-term toxicities, particularly affecting swallowing function, that have a negative effect on QOL. Patients recruited into PATHOS will undergo transoral surgery to resect their primary tumours as well as a neck dissection. Post-operatively, they will be stratified into risk groups according to the presence or absence of pathological risk factors for recurrence. The aim of PATHOS is to determine whether reducing the intensity of adjuvant treatment after minimally invasive surgery in HPV-positive OPSCC, either by lowering RT dose in intermediate-risk patients or omitting chemotherapy in high-risk patients will result in better swallowing function, whilst maintaining excellent clinical outcomes. The primary outcome of the PATHOS phase II study will be long-term patient reported swallowing function measured using the MDADI score at 12 months post-treatment. Secondary outcomes will include local control rates and survival as well as a panel of objective and self-reported swallowing assessments. If the phase II study is successful, PATHOS will continue to a phase III study. The primary outcome of the proposed phase III study will be overall survival.

## Methods/Design

### Study design

PATHOS is a multicentre, open label, parallel group phase II/III RCT funded by Cancer Research UK (CRUK). Patients must have biopsy proven OPSCC and should be clinically staged T1–T3 N0-N2b M0. Their primary tumour must be considered resectable via a transoral approach as determined by the local Multidisciplinary Team (MDT). HPV-positivity will be confirmed by central testing of diagnostic biopsy specimens by p16 immunohistochemistry and high risk HPV in-situ hybridisation. Synchronous neck dissection will be undertaken as per standard protocols depending upon the volume of regional metastatic disease. Following surgery, patients will be allocated into study groups based on histological findings (Fig. 1):

**Fig. 1 Fig1:**
[figure not shown]
Trial schema

Group A: Patients whose tumours have no adverse histological features will not receive any adjuvant treatment as per standard of care.

Group B: Patients with T3 tumours (or T1–T2 tumours with additional risk factors), N2a (metastasis in single ipsilateral node 31–60 mm diameter) or N2b (metastasis in multiple ipsilateral nodes <61 mm diameter), tumours with evidence of perineural and/or vascular invasion, or close margins (1–5 mm) around the primary tumour specimen but with negative marginal biopsies and no evidence of cervical lymph node ECS. Patients in this group will be randomised to either post-operative RT 60Gy in 30 fractions over 6 weeks (Control Arm B1) or post-operative RT 50Gy in 25 fractions over 5 weeks (Test Arm B2).

Group C: Patients with tumours of any T or any N stage with the following high risk pathological features: positive (<1 mm) margins around the primary tumour (but with negative marginal biopsies) and/or evidence of cervical lymph node ECS. Patients in this group will be randomised to either post-operative CRT 60Gy in 30 fractions over 6 weeks with concurrent cisplatin (Control Arm C1) or post-operative RT 60Gy in 30 fractions over 6 weeks without chemotherapy (Test Arm C2).

### Participating sites

The phase II trial will recruit at over approximately 20 sites in the UK. Participating sites will be required to complete a registration form to confirm that they have adequate resources and experience to conduct the trial. The planned phase III trial will recruit across Europe.

### Participant eligibility

Participants are eligible to enter the trial pre-operatively if they meet all of the inclusion criteria and none of the exclusion criteria (Table 1). Post-operatively, patients allocated to Groups B and C on the basis of their pathology must re-confirm their consent for the study and will be assessed for their suitability for adjuvant treatment. Patients in Group B must be fit to undergo RT. Patients in Group C must be fit to undergo CRT and meet additional criteria as per Table 2.

**Table 1 Tab1:** Inclusion and exclusion criteria for all patients in PATHOS trial

Inclusion criteria for all patients	
1.	Histologically confirmed diagnosis of OPSCC
2.	HPV-positive on central testing
3.	Stage T1-T3, N0-N2b tumours (based on cross-sectional imaging investigations carried out within 6 weeks of study entry)
4.	Local MDT decision to treat with primary transoral resection and neck dissection
5.	Fit for surgery and adjuvant treatment as assessed by the local MDT
6.	Aged 18 or over
7.	Able to provide written informed consent
Exclusion criteria for all patients	
1.	HPV-negative tumours
2.	Stage T4 tumours and/or T1–T3 tumours where transoral surgery is considered not feasible
3.	N2c–N3 nodal disease
4.	Unresectable retropharyngeal node involvement
5.	Current smokers with N2b disease including smokers up to 2 years before diagnosis
6.	Any pre-existing medical condition likely to impair swallowing function and/or a history of pre-existing swallowing dysfunction prior to index oropharyngeal cancer
7.	Patients with distant metastatic disease (stage IVc)
8.	Patients with a history of malignancy in the last 5 years, except basal cell carcinoma of the skin or carcinoma in-situ of the cervix
9.	Women who are pregnant or breastfeeding and fertile women who will not be using contraception during the trial

**Table 2 Tab2:** Additional inclusion and exclusion criteria for patients in Group C

Inclusion criteria for patients in Group C	
1.	Bone marrow reserve adequate for chemotherapy (i.e. absolute neutrophil count (ANC) ≥ 1.5 × 10^9^/l and platelet count ≥ 100 × 10^9^/l)
2.	Adequate creatinine clearance defined as GFR ≥ 50 ml/min
Exclusion criteria for patients in Group C	
1.	History of significant cardiac or other medical conditions that preclude the use of cisplatin and intravenous hydration
2.	Clinically significant hearing impairment sufficient to affect daily living and/or pre-existing tinnitus
3.	Pre-existing peripheral neuropathy that precludes the use of cisplatin
4.	Hypersensitivity to the active substance or other platinum compounds or to any of the other excipients
5.	Dehydrated condition

### Method of randomisation

Patients in Groups B and C will be randomised to a trial arm using the method of minimisation with a random element. Randomisation will be performed centrally by the Wales Cancer Trials Unit (WCTU). Participants will be stratified prior to randomisation by T stage, N stage, smoking history and treating centre.

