#### Radiotherapy

Patients should start RT within 5 weeks and no later than 6 weeks from surgery, so that combined treatment (surgery and RT) is completed within 11 weeks to avoid poor LC and survival rates that result from protracted treatment [11]. Patients are managed as category 1 as per the Royal College of Radiologists Guidelines and RT should be completed within 6 weeks for patients having 60Gy in 30 fractions and within 5 weeks for those having 50Gy in 25 fractions [27].

The primary tumour should be categorised as lateralised or non-lateralised based on clinical and radiological assessments.Lateralised tumour: Tonsillar tumour confined to the tonsillar fossa or extending onto or into the adjacent base of tongue and/or soft palate by less than 1 cm.Non-lateralised tumour: Tonsillar tumour that involves the adjacent base of tongue and/or soft palate by more than 1 cm or a tumour that arises from a midline structure (base of tongue, soft palate, posterior pharyngeal wall).

Patients with lateralised tumours should undergo unilateral neck RT, regardless of the nodal stage of the ipsilateral neck. Patients with non-lateralised tumours should undergo bilateral neck RT, except in cases where they have undergone contralateral selective neck dissection and pN0 status is confirmed on that side (see above).

PATHOS uses a geometric approach to define target volumes. Pre-operative imaging, pan-endoscopy reports, operative findings and pathology information should be used to delineate target volumes. The Clinical Target Volume 1 (CTV1) includes the primary and nodal tumour beds with a margin (1–1.5 cm) and all pathologically involved nodal levels. Arms B1, C1, C2 receive 60Gy/30 fractions and Arm B2 receives 50Gy/25 fractions. The Clinical Target Volume 2 (CTV2) includes all at risk uninvolved nodal levels that require prophylactic RT. Arms B1, C1, C2 receive 54Gy/30 fractions and Arm B2 receives 50Gy/25fractions. Some centres may, *a priori* opt to boost high-risk sub-volume(s) for patients in Group C to 66Gy/30 fractions. Neck node levels for prophylactic RT should be outlined according to updated consensus guidelines and atlas [28]. A margin (3–5 mm) will be added to each CTV to produce the respective Planning Target Volume.

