### Statistical analyses

Mean MDADI scores at 12 months will be compared between arms using either a t-test or nonparametric methods depending upon distributions. We will adjust for the randomisation stratification variables using regression techniques. This primary analysis will be conducted when the last patient has had their 12 month assessment. An Independent Data Monitoring Committee will review the accumulating data (survival, toxicities, recruitment) at 6 monthly intervals. Strict monitoring has been built in for recurrence. A formal interim analysis will be performed after 38 patients have been randomised in each randomisation (19 per arm), treated and followed up for 6 months. Within each randomisation, a stopping rule will be based on observing an absolute observed difference of 6 or more locoregional recurrences and/or deaths in either of the intervention arms. For swallowing endpoints, subgroup analysis by T stage and tumour subsite (tonsil, soft palate, tongue base) will be carried out, as the most likely relevant clinical co-variables affecting swallowing function*.*

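### The primary MDADI regression omits planned neck radiotherapy laterality, a likely swallowing covariate that can be recorded before randomisation; the cost is a modest loss of precision, not bias

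*Protocol article*

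**What the plan says.** Method of randomisation describes minimisation with a random element: "Participants will be stratified prior to randomisation by T stage, N stage, smoking history and treating centre". Statistical analyses gives the phase II primary comparison: "Mean MDADI scores at 12 months will be compared between arms using either a t-test or nonparametric methods depending upon distributions". It then states the adjustment: "We will adjust for the randomisation stratification variables using regression techniques". The same section singles out T stage and tumour subsite (tonsil, soft palate, tongue base) as the clinical factors most likely to affect swallowing, and plans subgroup analyses by both. T stage is also balanced and adjusted for; subsite is not.

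The Radiotherapy section defines laterality: "The primary tumour should be categorised as lateralised or non-lateralised based on clinical and radiological assessments". For one class, "Patients with lateralised tumours should undergo unilateral neck RT, regardless of the nodal stage of the ipsilateral neck". For the other, "Patients with non-lateralised tumours should undergo bilateral neck RT, except in cases where they have undergone contralateral selective neck dissection" and that side is confirmed pN0. Tumours of the tongue base, soft palate or posterior pharyngeal wall are non-lateralised by definition; tonsillar tumours can fall either way, depending on a 1 cm extension threshold.

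The Background, under Dysphagia after treatment, gives the link to the endpoint: "Dysphagia after RT has been shown to correlate with increased mean doses of radiation to swallowing-related organs".

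**The concern.** The phase II endpoint is patient-reported swallowing, and the article's own account ties long-term dysphagia to radiation dose in swallowing structures. The extent of the neck field plausibly affects that dose, and the Radiotherapy section says these structures are not used in plan optimisation, so planning is not asked to offset a wider field. Laterality is therefore a natural baseline covariate for MDADI.

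It is also available in time. The classification rests on clinical and radiological findings, and any contralateral dissection is done at surgery. Randomisation follows the pathology-based allocation to Group B or C.

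At stake is efficiency. With about 37 analysed patients per arm in each randomisation, variance explained by laterality stays in the error term when one covariate could remove it. The phase II result decides whether phase III goes ahead, so precision that costs almost nothing is worth having.

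**Working it through.** **Inputs from the article (Sample size calculation, Phase II; Statistical analyses):** target difference 10 MDADI points; two-sided alpha 5%; power 80%; 148 evaluable, 74 per randomisation. Equal allocation is inferred from the interim rule's 19 per arm, giving 74/2 = 37 per arm.

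**Assumptions, not in the article:** MDADI SD 15; bilateral share p = 0.3 to 0.5; MDADI difference between bilateral and unilateral treatment g = 5 to 10 points.

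**1. The plan's own figure.** The article states no SD. With SD 15, a two-sample t calculation for 10 points at 80% power needs 37 per arm, or 74 per randomisation and 148 in all. Solving backwards from 37 per arm gives an SD of 15.15 (t) or 15.35 (normal approximation). Allowing for 20% loss, 74/0.8 = 92.5, rounded up to 93 per randomisation and 186 in total, as stated. The sample size is not in question.

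**2. Precision without laterality.** SE = SD × sqrt(2/n) = 15 × sqrt(2/37) = 3.49 points. Power at 37 per arm is 80.8%.

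**3. Precision with laterality as a covariate.** R² = p(1 − p)g²/SD²; residual SD = SD × sqrt(1 − R²); power from the noncentral t with one further degree of freedom spent.

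| p | g | R² | SE | Power at 37 per arm | n per arm for 80% |
|---|---|---|---|---|---|
| 0.3 | 5 | 0.21 × 25/225 = 0.023 | 3.45 | 81.6% | 36 |
| 0.3 | 10 | 0.21 × 100/225 = 0.093 | 3.32 | 84.4% | 34 |
| 0.5 | 5 | 0.25 × 25/225 = 0.028 | 3.44 | 81.8% | 36 |
| 0.5 | 10 | 0.25 × 100/225 = 0.111 | 3.29 | 85.1% | 33 |

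**4. Chance imbalance.** If laterality is left to chance, the between-arm difference in bilateral share has SD sqrt(2p(1 − p)/37) = 0.107 (p = 0.3) to 0.116 (p = 0.5). From two independent binomials of size 37, the chance of a difference of at least 10 percentage points is 37-42%, and of at least 20 points 6-8%. The resulting shift in the mean MDADI difference has SD 0.107 × 5 = 0.5 to 0.116 × 10 = 1.2 points.

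**5. Is that shift extra error?** No. For p = 0.5 and g = 10, the squared adjusted SE plus the squared shift SD is 3.29² + 1.16² = 10.8 + 1.3 = 12.2, which is 3.49². The unadjusted SE already contains the imbalance; adjustment removes that component.

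**The case against.** **A covariate list can be left to the analysis plan.** The article does not say that other covariates are excluded, and an unseen plan may add laterality. If it does, the covariate part of this point is met. But the article does name an adjustment set for the primary analysis, and laterality and subsite are not in it.

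**Swallowing was not ignored in the design.** A reader might infer that the balancing factors were chosen only for tumour prognosis. The article does not support that: it names T stage as a likely swallowing covariable and both balances and adjusts for it. It also plans subsite subgroups and a correlation of swallowing outcomes with dose to the swallowing structures. This stands, although neither of those analyses reduces the error variance in the main comparison.

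**The link is inferred.** A reader might say that laterality sets the dose to swallowing structures. The article does not quantify how laterality changes that dose or MDADI, and the primary tumour bed is treated in either case. Only a plausible effect can be claimed.

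**The gain could be smaller than shown.** The working starts from an unadjusted comparison. The plan already adjusts for T stage and centre, and contralateral dissection is a centre option, so part of the laterality effect may already be captured. In the other direction, a 15-point effect with half bilateral would take power to about 90%, but that effect is larger than the 10-point difference the trial is designed to detect.

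**The minimisation factors are defensible.** With about 93 patients per randomisation, four factors and some 20 sites, a fifth factor is a trade-off. T stage, N stage and smoking also suit the planned phase III survival endpoint.

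**Classification with the arm known.** Because the trial is open label, a reader might infer that laterality could be judged after allocation. Nothing in the article suggests this happens; the criteria do not depend on the arm. It is a reason to record the field early and not a fault in itself.

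**Conclusion.** The point holds as a modest improvement in efficiency. The stated adjustment set omits planned neck radiotherapy laterality, and also subsite, although the article's own reasoning makes them relevant to the endpoint and laterality can be known before randomisation.

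Under an assumed SD of 15, 30-50% bilateral and a 5-10 point laterality effect, adjustment would raise power at 37 per arm by about 1 to 4 percentage points, from about 81% to about 82-85%. Equivalently, 33-36 per arm would give the planned 80%. Overlap with T stage and centre would reduce this.

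It would be wrong to conclude that the MDADI comparison is biased or that the 80% power fails. Randomisation keeps the comparison unbiased, and the chance imbalance already lies within the SE of about 3.5 points.

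**What to change.** Record planned neck radiotherapy (unilateral or bilateral, allowing for a contralateral dissection confirmed pN0) on the randomisation form before allocation. Add it as a prespecified binary covariate in the primary MDADI regression, alongside the stratification variables. Classifying at that point also makes it a baseline variable beyond dispute.

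Adding laterality as a minimisation factor is optional and not required.

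The cost is one form field and one degree of freedom in each randomisation's model. No patients, visits or procedures are added, and treatment does not change. If laterality proves unrelated to MDADI, the loss is that one degree of freedom.
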